## Abstract

**Background:**

Individuals with chronic lung disease are more susceptible to present reduction in exercise tolerance and muscles strength not only due to pulmonary limitations but also due systemic repercussions of the pulmonary disease.

The aim of this study is to assess the physical capacity, peripheral muscle function, physical activity in daily life, and the inflammatory markers in children and adolescents with asthma after pulmonary rehabilitation program.

**Method:**

This is a study protocol of randomized controlled trial in asthmatic patients between 6 to 18 years old. The assessments will be conducted in three different days and will be performed at the beginning and at the end of the protocol. First visit: quality of life questionnaire, asthma control questionnaire, pre- and post-bronchodilator spirometry (400 μcg salbutamol), inflammatory assessment (blood collection), and cardiopulmonary exercise test on a cycle ergometer to determine aerobic capacity. Second visit: assessment of strength and endurance of the quadriceps femoris and biceps brachii muscles with concomitant electromyography to assess peripheral muscle strength. Third visit: incremental shuttle walk test (ISWT) and accelerometer to evaluate functional capacity and physical activity in daily life during 7 days. Then, the volunteers will be randomized to receive pulmonary rehabilitation program (intervention group) or chest physiotherapy + stretching exercises (control group). Both groups will have a supervised session, twice a week, each session will have 60 minutes duration, with minimum interval of 24 hours, for a period of 8 weeks. Intervention group: aerobic training (35 minutes) intensity between 60 to 80 % of the maximum workload of cardiopulmonary exercise testing or of ISWT; strength muscle training will be applied to the quadriceps femoris, biceps brachii and deltoid muscles (intensity: 40 to 70 % of maximal repetition, 3 x 8 repetition); finally the oral high-frequency oscillation device (Flutter®) will be used for 5 minutes. The control group: oral high-frequency oscillation device (Flutter®) for 10 minutes followed by the stretching of upper and lower limbs for 40 minutes. It is expected to observe the improvement in aerobic capacity, physical activity in daily life, muscle strength and quality of life of patients in the intervention group, and reduction in inflammatory markers.

**Trial registration:**

Clinical Trial Number: NCT02383069. Data of registration: 03/03/2015

## Background

Asthma is one of the main chronic diseases in childhood. It is characterized by inflammation of the airways [1]. Individuals with chronic lung disease are more susceptible to present reduction in exercise tolerance, not only due to ventilatory constraints, but also due to systemic manifestations of pulmonary disease [2]. Thus, the more severe and the less controlled the disease, the higher the dyspnea and fatigue reported by patients. In general, the obstruction increases the airways resistance, hindering the physiological ventilatory response during physical exertion and leading to dyspnea [2]. This in turn leads to the patient having a more sedentary lifestyle, predisposing them to early fatigue and exercise intolerance.

Cardiopulmonary exercise testing (CPET) is the gold standard for determining exercise intolerance [3, 4]. As it is a high-cost assessment, few studies have used CPET as a method to evaluate asthmatic children and adolescents [5–9]. Villa and colleagues [6] described the reduction of oxygen uptake (VO_2peak_ ) in patients with moderate/severe asthma when compared to the control group. The same was observed by an English group that found VO_2max_ reduction in the asthmatic group [7, 8]. Those authors proposed that asthma severity could be an important factor in determining aerobic capacity. Some limitations were observed in those mentioned studies, such as not measuring asthma control (a factor that may influence the patient’s condition), the small number of assessed individuals, and not determining the corticosteroid dose used by patients with asthma.

Clinical field tests are a less expensive alternative to CPET in determining functional capacity. The incremental shuttle walking test (ISWT) is a simple and inexpensive test described by Singh and colleagues [10]. Several authors using ISWT assessment found a reduction in the functional capacity of adults with chronic lung disease and its association with lung function and quality of life [11–13]. To our knowledge, only Ahmaidi and colleagues [14] have used the run shuttle walk test in pediatric patients with asthma to determine their functional capacity by comparing with CPET.

Reduction in peripheral muscle strength has been described in patients with cystic fibrosis [15] and asthma [6], and the hypothesis for that is that it is due to sedentary lifestyle, the chronic use of medication, and systemic inflammation. To our knowledge, there are no studies evaluating muscle strength and peripheral muscle endurance by using electromyography in asthmatic children.

Some studies have had interesting results in cardiopulmonary conditions, quality of life, and reduction in the number of hospitalizations after a pulmonary rehabilitation program in asthmatic children and adolescents [14, 16–23]. Wanrooij and colleagues [24] carried out a systematic review of physical training with asthmatic children and adolescents, and concluded that physical activity should be recommended to this population, although some issues have not yet been clarified due to limitations in the clinical trials. The control of the disease has not been addressed by specific questionnaires in any study. The assessment of inflammatory markers has rarely been addressed [21], neither has quality of life after physical training [20, 21].

Hence, the current study aims to assess physical capacity, peripheral muscle function, physical activity in daily life, quality of life, and inflammatory markers in children and adolescents with asthma, after undergoing a pulmonary rehabilitation program.

## Methods

### Study design

This is a randomized clinical trial to be conducted in the pulmonary rehabilitation laboratory at University Nove de Julho. Clinically diagnosed asthmatic patients will be recruited in the Allergy, Clinical Immunology and Rheumatology Clinic at the Department of Pediatrics of Sao Paulo School of Medicine, Federal University of Sao Paulo. The individuals will be enrolled in the study after their legal guardians have read, agreed to, and signed the informed consent form. The current project was approved by the Associacao Educacional Nove de Julho Ethical Committee, Sao Paulo, Brazil, number 738192/2014.

The study will include patients diagnosed with asthma, between 6 and 18 years old, who are under medical treatment and disease control according to the Global Initiative for Asthma (GINA) criteria [1]. Those who fail to carry out the protocol evaluations, who interrupt medical care and/or drug-based treatment, who present with acute lung infection, other chronic lung diseases, or other comorbidities (neuropathies, heart disease), and those who miss more than 20 % of the rehabilitation sessions will be excluded from the study.

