### Intervention group

The intervention group will have a supervised rehabilitation program held twice a week. Each session will be 60 minutes in duration, with a minimum interval of 24 hours, for a period of 8 weeks. Each session will consist of three parts: aerobic training, strength muscle training, and chest physiotherapy. The aerobic training will be held for 35 minutes (10 minutes of warm up, 20 minutes on target load, and 5 minutes of cooling down) with an initial intensity of 60 % of the maximum load obtained in the maximal cardiopulmonary exercise testing or in the ISWT. The intensity will be gradually increased up to 80 %, so that fatigue or dyspnea values are kept between 4 and 6, according to the modified Borg scale [31]. When necessary, supplemental oxygen will be supplied during training to keep oxygen saturation greater than 92 %. Strength muscle training will be applied to the quadriceps femoris, biceps brachii, and deltoid muscles for 15 minutes. The intensity will be 40 to 70 % of maximal repetition (1 MR) in three sets of eight repetitions. Finally, for chest physiotherapy, the oral high-frequency oscillation device (Flutter®) will be used for 5 minutes. The volunteers in this group will receive a 200-μcg bronchodilator before starting the session each day.

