### Control group

The control group will have chest physiotherapy and stretching exercises twice a week. Each session will be 60 minutes, with a minimum interval of 24 hours, for a period of 8 weeks. For each session, the oral high-frequency oscillation device (Flutter®) will be used for 10 minutes, 5 minutes in each lateral decubitus position, followed by stretching of the upper and lower limbs for 40 minutes. All exercises will be active, performed in sitting and lying positions without increasing the heart rate. The remaining 10 minutes will be used to discuss doubts about the disease and the use of the booklet.

Both groups will be oriented about the disease (proper use of medication, use of peak flow, triggering factors for crisis). On the date of the initial evaluation, they will take home a booklet with the main information about the given guidelines. All volunteers will be reevaluated after 8 weeks, when the same initial assessments will be performed again.

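### The attendance rule removes children after randomisation, so the groups compared need not be the groups randomised

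*Protocol article*

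**What the plan says.** The exclusion list is in the Study design section of the protocol article. It ends with an attendance rule: children who miss more than 20 % "of the rehabilitation sessions will be excluded from the study". The same sentence also lists "Those who fail to carry out the protocol evaluations, who interrupt medical care and/or drug-based treatment, who present with acute lung infection", followed by other chronic lung diseases and comorbidities. It does not say whether these other clauses apply before or after allocation.

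The Abstract (Method) describes three assessment visits and continues: "Then, the volunteers will be randomized to receive pulmonary rehabilitation program (intervention group) or chest physiotherapy + stretching exercises (control group"). Both programmes run for 8 weeks. For training, "The intervention group will have a supervised rehabilitation program held twice a week". For control, "The control group will have chest physiotherapy and stretching exercises twice a week".

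On follow-up, the Control group section says: "All volunteers will be reevaluated after 8 weeks, when the same initial assessments will be performed again". The Statistical analysis section plans comparisons between groups and over time. It names no analysis set and does not say how children excluded under the attendance rule are handled.

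**The concern.** Attendance cannot be an eligibility condition, because no session exists until a child has been allocated. A rule that takes poor attenders out of the study therefore acts on the randomised groups and changes who is compared.

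This matters if the reasons for missing sessions differ between arms and are related to the outcome. The article gives grounds to expect that they might:

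- Training is done at 60 to 80 % of maximum load, with dyspnea or fatigue scores kept at 4 to 6. Control sessions consist of the Flutter device and stretching that is meant not to raise the heart rate.
- The Background links more severe and less controlled asthma to more dyspnea and fatigue. The primary outcome is physical capacity.
- The exclusion rule speaks of rehabilitation sessions, and the article uses the term rehabilitation program for the intervention arm only. Read literally, the rule could remove children from one arm and not the other.

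At stake is whether the primary comparison keeps the protection of randomisation.

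**Working it through.** **1. When the rule acts.** The order in the Abstract is baseline visits, randomisation, sessions, reassessment. The attendance rule can be met only in the third step.

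**2. Threshold.** Sessions: 2 per week × 8 weeks = 16. The limit is 0.20 × 16 = 3.2. Missing 3 (18.75%) is allowed and missing 4 (25%) triggers exclusion. A child excluded for missing exactly 4 has attended 12 of 16.

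**3. Conflict in the text.** Study design removes some randomised children from the study. The Control group section reassesses all volunteers at 8 weeks. Unless volunteers there means only those still in the study, both statements cannot be followed.

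**4. Difference between attenders and all randomised (illustration).** From the Statistical analysis section: planned difference 2.0 levels. Assumed, because the article gives no figures: a share p = 0.20 of the training arm is excluded, these children have a fraction f of the gain, and controls are unaffected.

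All-randomised effect = (1 − p) × 2.0 + p × f × 2.0

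- f = 0.5: 1.6 + 0.2 = 1.8 levels
- f = 0: 1.6 + 0 = 1.6 levels

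The retained children show 2.0, so the gap is 0.2 to 0.4 levels.

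**5. Selection when training has no effect (simulation).** Assumed: 33 per arm (half of the stated total of 66), SD 1.6, 4,000 replicates. The children with the poorest prognosis are excluded, and prognosis correlates 0.3 or 0.5 with the outcome.

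| Excluded, training / control | Spurious difference (levels) | Type I error |
|---|---|---|
| 20% / 20% | about 0 | 5.2% |
| 30% / 10% | +0.14 to +0.24 | 6.4% to 8.4% |
| 20% / 0% | +0.17 to +0.27 | 7.2% to 9.6% |
| 10% / 30% | −0.13 to −0.24 | 5.8% to 8.2% |

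The sign depends on which arm loses more children, and the article does not say.

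**6. Does the planned size depend on the exclusion?** The stated 27 per group does not reproduce from the stated inputs. With the 80% read as power and a two-sided 5% test, n = 2 × (1.96 + 0.84)² × (1.6/2.0)² ≈ 10.04, rounded up to 11 per group. That discrepancy is a separate matter. For the present question, take 30 per group and SD 1.6. The standard error is 1.6 × √(2/30) = 0.413, and power ≈ Φ(δ/0.413 − 1.96).

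- δ = 1.8: Φ(2.40) ≈ 99%
- δ = 1.6: Φ(1.91) ≈ 97%

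On the article's own inputs, analysing everyone costs little power.

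**The case against.** The strongest reply is that a journal article may leave the analysis set to the full protocol or an analysis plan. That would answer a complaint that intention-to-treat is not mentioned. It does not answer a stated rule that takes randomised children out of the study: if they leave before reassessment, no later plan can recover their 8-week data.

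Other objections do stand, and they limit the point:

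- **Direction.** A reader might infer that the result must favour training. The article does not show this. Session frequency, length and duration are the same in both arms, and training load is tied to the child's symptom score. With equal exclusion the simulated selection bias is about zero, and with more exclusions among controls it reverses.
- **Size.** A reader might take the 1.6-level case as the expected distortion. It assumes no gain at all in children who may have attended 12 of 16 sessions. The illustration also contrasts two target effects, attenders and all randomised. It does not measure bias from lost randomisation.
- **The other clauses.** A reader might count failed evaluations, interrupted treatment and acute lung infection as further post-randomisation exclusions. Each can be read as a baseline criterion, and infection stands beside chronic lung disease and heart disease. Nothing confines them to baseline either, and the evaluations are repeated at 8 weeks. Their timing is unclear.
- **Removal for lack of benefit.** No criterion excludes a child because training did not help.
- **Loss allowance.** The allowance for potential losses is unspecified and may already cover these exclusions.

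**Conclusion.** The point holds for the attendance rule. As written, it removes randomised children who miss 4 or more of 16 sessions. It makes the compared groups differ from the randomised ones, and it conflicts with the promise to reassess all volunteers. This follows from the article's text and rests on no assumed figure.

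The consequence is a possible bias in the primary comparison. Bias towards training is plausible given the unequal physical demands and the possibly one-armed wording. The article contains no attendance data, so neither direction nor size can be determined. The figures of 1.8 or 1.6 against 2.0 levels depend wholly on the assumed 20% exclusion and the assumed half or zero gain. For the other three clauses, the finding is only that their timing needs to be stated.

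**What to change.** - Limit the exclusion criteria to conditions present before randomisation. State for failed evaluations, interrupted treatment and acute lung infection whether each applies before or after allocation.
- Reconcile the Study design and Control group sections so that every randomised child is invited to the 8-week reassessment whatever the attendance.
- Define the primary analysis as all randomised children in their allocated group, and state the method for missing 8-week data. Without such a method, a child with no second test still drops out of a pre/post analysis.
- Keep the children attending at least 80% of sessions (13 or more of 16) as a labelled per-protocol sensitivity analysis, with the same definition in both arms.

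The cost is a change of wording plus the reassessment of poor attenders, which the Control group section already foresees. The estimated effect may be smaller. On the stated inputs no extra children are needed.

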### Outcomes

The primary outcome will be the physical capacity assessed by the cardiopulmonary exercise testing and ISWT. The secondary outcomes will be quality of life, peripheral muscle strength, and inflammatory markers.

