#### Cardiopulmonary exercise testing

The exercise test will be performed in an electromagnetic braking cycle ergometer (Corival®, LODE BV Medical Technology, Groningen, Netherlands) connected to a system composed of gas exchange and ventilatory variables being analyzed breath by breath (Breeze CardiO_2_ System® microcomputer; Medical Graphics Corporation-MGC, St Paul, MN, USA). After 2 minutes of freewheel load, the load will be increased (5 to 20 watts/minute) and the test will be limited between 8 and 12 minutes [29, 30]. The following measurements will be analyzed: oxygen consumption (VO_2_, mL min^−1^) and carbon dioxide production (VCO_2_, mL.min), minute ventilation (V_E_, L/minute), tidal volume (TV) (mL), respiratory rate (f) (respirations/minute), and ventilatory equivalents for O_2_ and CO_2_ (V_E_/VO_2_, V_E_/VCO_2_). The heart rate (HR), pulse oxyhemoglobin saturation (SpO_2_) will be continuously recorded. Blood pressure (BP) will be measured every 2 minutes of exercise. Dyspnea (Borg D) and lower limb fatigue (Borg LL) perception scores will be assessed by using the modified Borg scale [31], with the patient at rest and immediately after the exercise cessation. The test will be interrupted by the child or adolescent due to intolerable dyspnoea and/or fatigue making it impossible to progress the workload. On the other hand, the test will be stopped if SpO_2_ is ≤82 %, or if patients have cardiac arrhythmias or abnormal blood pressure response.

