#### Incremental shuttle walking test (ISWT)

The ISWT will be held in a 10-m-long corridor according to the original description [10]. It is a test externally cadenced by an audible signal, in which the speed increases every minute ranging from 1.79 to 10.2 Km/h. The test comes to the end when the patient is not able to reach the cone two consecutive times, or the patient needs to stop the test due to fatigue or breathlessness, or SpO_2_ falls below 82 %. The tests will be performed twice on the same day, with a 30-minute break between them. Heart rate, blood pressure, and Borg fatigue and Borg dyspnea will be evaluated at the beginning and at the end of the test. The total test time and the distance walked by the patient will be recorded at the end of the test.

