### Statistical analysis

The sample size was based on the run shuttle walk test levels and on the maximum load achieved in CPET [14]. Considering the stages of the shuttle, and assuming an alpha risk of 5 % and beta risk of 80 %, standard deviation of 1.6, and a difference in magnitude of 2.0 levels before and after the pulmonary rehabilitation program [14], the sample size needed was 27 patients in each group. Considering the load (W) achieved in the cardiopulmonary exercise testing, with a −3 ± 2 W difference pre- and post-intervention in the control group, and of 16 ± 7 [20] in the intervention group, with an alpha risk of 5 % and a beta risk of 95 %, the sample size needed was 10 patients in each group. Therefore, considering potential losses, 30 asthmatic patients will be recruited for each group, requiring a total of 66 volunteers.

The data normality will be analyzed using the Kolmogorov-Smirnov test. Parametric data will be represented as means (SD) and nonparametric data as medians (IQR (25th−75th percentiles ). Comparisons between groups and time (pre- and post-rehabilitation) will be analyzed by two-way analysis of variance (ANOVA), with the Bonferroni test post hoc, or by the Kruskal Wallis test, depending on the data adherence or non-adherence to the Gaussian curve. Correlation between variables will be analyzed by Pearson or Spearman correlation according to the data distribution. Three-way repeated measures ANOVA group vs endurance (0–100 % endurance time, 25 % increments time) vs time (pre- and post-) will be used to assess the dependency of the EMG variables and will followed by post hoc Student–Newman–Keuls pairwise comparisons, when appropriate. The value of *P* <0.05 will be set as significant. SPSS version 13 (Chicago, IL, USA) will be the statistical software used in the study.

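### The primary outcome names two exercise tests but no variable and no success rule, under one 5% threshold, and the sample size rests on measures that neither test section lists

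*Protocol article*

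**What the plan says.** - **Outcomes:** "The primary outcome will be the physical capacity assessed by the cardiopulmonary exercise testing and ISWT". Quality of life, peripheral muscle strength and inflammatory markers are secondary.
- **Cardiopulmonary exercise testing:** the list opens "The following measurements will be analyzed: oxygen consumption" and goes on to carbon dioxide production, minute ventilation, tidal volume, respiratory rate and the two ventilatory equivalents. That makes seven measurements, unranked. Maximum load is not among them.
- **Incremental shuttle walking test (ISWT):** "The total test time and the distance walked by the patient will be recorded at the end of the test". Level reached is not listed.
- **Statistical analysis, sizing:** "The sample size was based on the run shuttle walk test levels and on the maximum load achieved in CPET". There is one calculation per test, giving 27 per group for shuttle levels and 10 per group for load.
- **Statistical analysis, testing:** one significance threshold of 0.05 for the study. Bonferroni appears as the post hoc test after the two-way ANOVA, and Student–Newman–Keuls after the EMG ANOVA. No order, alpha split or both-must-succeed rule is given for the primary outcome.

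**The concern.** Physical capacity is a construct, and two tests are offered to measure it. The Abstract gives them different jobs: CPET for aerobic capacity and the ISWT for functional capacity. They could therefore disagree, and the text does not say what the trial would then conclude. If a significant result on either one counts, a positive claim carries more than a 5% error rate. The Bonferroni step does not help, because it works among the group and time comparisons for a single variable, not across variables.

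A second, separate problem concerns what the sample size refers to. A reader who wants to know which CPET variable and which ISWT variable the trial was powered for finds two measures in the sizing paragraph and different ones in the test sections. The primary outcome, the measurement lists and the sizing do not meet on a single named variable.

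**Working it through.** **1. The plan's own sample sizes.** Two equal groups, two-sided 5% assumed (the side is not stated), and the printed beta risk read as power. Formula: n per group = 2·SD²·(z₁₋α/₂ + z_power)² / δ².

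- Shuttle levels. Inputs: "assuming an alpha risk of 5 % and beta risk of 80 %, standard deviation of 1.6". The effect assumed is 2.0 levels, which the plan describes as a pre/post change. n = 2 × 1.6² × (1.960 + 0.842)² / 2.0² = 5.12 × 7.85 / 4 = 10.05, so 11 per group (12 by the t test). The plan states "the sample size needed was 27 patients in each group". The figure 27 appears only with inputs that are not stated, such as 99.5% power, or an SD of 1.6 × √2 with 90% power.
- Load. Inputs: "with a −3 ± 2 W difference pre- and post-intervention in the control group". For the other arm the plan takes a change of 16 W with SD 7, at 95% power. δ = 16 − (−3) = 19 W; SD = √((2² + 7²)/2) = 5.15. n = 2 × 26.5 × (1.960 + 1.645)² / 19² = 53 × 13.0 / 361 = 1.9, so 2 per group (4 by the t test; 4 to 5 if the SD is taken as 7). The plan states 10.

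Neither stated figure reproduces. That is a separate matter; it is shown here because the power figures in step 4 use the same inputs.

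**2. Error rate if either primary test suffices.** One variable per test, each at 0.05.

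- Independent statistics: 1 − (1 − 0.05)² = 1 − 0.9025 = 9.75%.
- Correlated statistics, by simulation of two normal statistics with |z| > 1.96. The correlations are assumptions.

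| Correlation | Chance of at least one false positive |
|---|---|
| 0 | 9.75% |
| 0.5 | 9.1% |
| 0.7 | 8.4% |
| 0.8 | 7.8% |
| 0.9 | 7.0% |

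If both tests had to succeed, having two tests would not take the error rate above 5%. The text does not state that rule.

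**3. Lists compared with sizing.**

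| Test | Listed in its own section | Used for sizing |
|---|---|---|
| CPET | seven gas-exchange and ventilatory measurements | maximum load (W) |
| ISWT | total time, distance | levels of the run shuttle walk test |

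ISWT speed rises every minute, so a level can be derived from total time. Maximum load must also be obtained, because the Intervention group section sets training intensity from it. Both measures can therefore be had, but neither is declared as an analysed endpoint.

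**4. Power if alpha is split, 0.025 per test.** (z for two-sided 0.025 is 2.241.)

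- Shuttle levels: n = 5.12 × (2.241 + 0.842)² / 4 = 12.2, so 13 per group. At 30 per group: 2.0 / (1.6 × √(2/30)) = 4.841; 4.841 − 2.241 = 2.600; power 99.5%.
- Load: n = 53 × (2.241 + 1.645)² / 361 = 2.2, so 3 per group. Power at 30 per group is essentially 100%.
- Sensitivity: if the shuttle SD should be 1.6 × √2 (one reading that yields 27), then 4.841 / √2 = 3.423. Power at 30 per group is Φ(3.423 − 2.241) = 88% at 0.025, against Φ(3.423 − 1.960) = 93% at 0.05.

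**The case against.** - **Sizing and type I error.** A reader might infer that the false-positive rate is uncontrolled because the sized variables differ from the listed ones. That does not follow. The mismatch unties the sample size from the endpoint and leaves type I error alone. This objection stands in full.
- **Counting every CPET output.** A reader might also treat all seven CPET measurements plus ISWT distance as rival primaries. Eight tests would give an error rate from 15.8% (correlation 0.8) to 33.7% (independence). The protocol does not support this. It makes physical capacity primary, not every CPET output, and the Background discusses aerobic capacity through peak or maximal oxygen uptake. Respiratory rate, tidal volume and the ventilatory equivalents are not natural measures of capacity. Several of these outputs are also built from one another, so independence is not credible. This objection stands too.
- **The mismatch may be an incomplete list.** Load and level are obtainable, and the sizing uses exactly one variable per test, which hints at what was intended. That makes the repair easy. It does not make either variable a declared endpoint, and the sizing refers to the run shuttle walk test from a cited study rather than to the ISWT described here.
- **The article is condensed.** A testing order or co-primary rule may sit in an analysis plan that is not shown, and the 0.05 per variable is read from a general threshold. This is fair as far as it goes. But naming the primary outcome is the protocol's task. The Outcomes section does it without a variable, and the conflict with the sizing paragraph is in the printed text.

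**Conclusion.** The point holds in two parts, which should be kept apart.

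First, the stated primary outcome and the single threshold do not hold a 5% error rate if either test may carry the claim. The rate is 9.75% under independence and 7% to 8% at correlations of 0.8 to 0.9. This assumes one variable per test and no both-must-succeed rule; the correlations are assumed. Choosing the CPET variable after seeing the data would push the rate higher, by an amount the protocol does not allow one to fix. The figures of 16% to 34% should not be quoted as the size of the problem.

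Second, the sample size refers to measures that neither test section lists. That is a defect of traceability, not of type I error.

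The trial remains feasible. The point should be settled before outcome data are examined, because without it the confirmatory claim is not protected.

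**What to change.** Issue a dated amendment before outcome data are examined; the Trial status section says recruitment has begun, so this is an endpoint clarification made during the trial.

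1. Name one primary variable per test: for example, peak load (W) for CPET, and either level reached (derived from total time) or distance for the ISWT. Other choices, such as peak oxygen uptake, are equally valid if fixed in advance.
2. Control the error across the two. Under Holm, the smaller p-value is tested at 0.025 and, if that succeeds, the other at 0.05. Alternatively, pre-state a fixed sequence with each test at 0.05. The sizing does not dictate the order: it uses both variables, and the shuttle calculation (27 against 10 per group) drives the sample.
3. If peak load is chosen, add it to the analysed CPET list. Make the remaining CPET variables secondary.
4. State that the shuttle sizing was borrowed from the run shuttle walk test, and how it relates to the ISWT measure chosen.

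**Cost.** No extra data. The amendment needs a dated justification, and the registry record must be brought into line with it. Under Holm, one test faces a slightly stricter threshold: power stays at about 99.5% or more with 30 per group on the protocol's own inputs, or about 88% for the shuttle test on the wider SD shown in the working. Under a fixed sequence, the second test can be claimed only if the first succeeds.
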